#### **9.3.1.1.2. Rash Treatment**

Antihistamines and topical corticosteroids may provide symptomatic relief to subjects who develop rash and experience associated symptoms such as pruritus.

Treatment of rash throughout the treatment period of the early access program should always follow generally accepted medical standards. In addition, the following treatment recommendations during telaprevir dosing should be followed.

Permitted topical and systemic antihistaminic drugs allowed for use with caution for all grades of rash include diphenhydramine (Benadryl®), hydroxyzine, levocetirizine (Xyzal®), and desloratadine (Clarinex®). Subjects should be followed symptomatically for possible increased exposure and worsening of adverse events such as drowsiness, and should be advised not to drive or operate heavy machinery while receiving antihistamines. The following antihistamines are prohibited from Day -14 until 7 days after the last dose of telaprevir: astemizole, terfenadine, and loratadine (see Section 8 and Attachment 2).

Because immunosuppression due to systemic corticosteroids can cause elevations in HCV RNA levels and because of the suspected drug-drug interactions between telaprevir and systemic corticosteroids, the latter should be used only when clinically necessary and after other treatments and measures have been employed, when possible. A consultation with a dermatologist should be requested for advice if needed. Telaprevir, Peg-IFN-alfa, and RBV must be discontinued immediately and permanently if a subject receives treatment with systemic corticosteroids (see also Section 10.2).

Topical corticosteroid use is permitted, but should be limited to brief periods, eg, up to 2 weeks of continuous/regular use, and limited to use on up to 50% of the body surface. Cream or lotion preparations are strongly encouraged in this situation, due to a lower absorption potential. Use of gel or ointment preparations of topical corticosteroids is discouraged due to a relative higher absorption potential. Treatment of skin eruptions with investigational agents or use of approved drugs in an off-label manner is also discouraged.

Use of all therapy (prescription and over-the-counter) for rash administered after the first use of telaprevir until 30 days after administration of the last dose of telaprevir, should be recorded on the appropriate pages of the CRF.

#### **9.3.1.1.3. Rash Management**

All skin events should be evaluated together with other systemic symptoms and laboratory abnormalities.

Management of rash until 30 days after the last telaprevir dose (Week 16 or earlier) should follow generally accepted medical standards, taking into account the protocol defined procedures described hereafter and treatment recommendations during telaprevir dosing described in Section 9.3.1.1.2. Management of rash during the subsequent weeks of treatment (standard treatment) should be in accordance with prescribing information recommendations for Peg-IFN-alfa and RBV.

Note that subjects having a skin rash (any grade) that requires treatment with systemic corticosteroids must have telaprevir, Peg-IFN-alfa, and RBV discontinued immediately and permanently. The sponsor's physician responsible for the early access program should be notified immediately of any subject who has a skin rash that requires treatment with systemic corticosteroids. The rash pages in the CRF must be completed.

Subjects experiencing any skin reaction considered to be a serious adverse event during telaprevir administration must permanently discontinue telaprevir treatment.

#### **9.3.1.1.3.1. Management of Grade 1 or 2 Rash**

General recommendations: For subjects experiencing a grade 1 or 2 rash, medical management will be at the discretion of the investigator and should follow generally accepted medical standards. Drugs to help alleviate symptoms as described above may be employed. In addition, subjects experiencing skin rash or pruritus should be advised of other strategies to minimize the intensity or progression of their signs and symptoms (eg, limiting sun exposure and heat; baking soda or oatmeal baths; loose-fitting clothes). Rash associated with RBV may complicate the assessment of rash in subjects receiving telaprevir. In all cases, subjects should be closely monitored for any rash progression or worsening of signs or symptoms of systemic involvement, and should be followed until the rash has resolved completely (in some cases this may require follow-up beyond the planned Follow-up Visit).

Study drugs discontinuation: For subjects experiencing a grade 1 rash, discontinuation of telaprevir, Peg-IFN-alfa, and RBV is generally not necessary. However, for subjects experiencing a grade 2 rash that progresses or does not improve, discontinuation of telaprevir, Peg-IFN-alfa, and RBV should be considered. If discontinuation of treatment due to rash is necessary, telaprevir should be permanently discontinued first. If the rash does not improve, symptomatically or objectively, within 7 days following telaprevir discontinuation, RBV use should be interrupted. Interruption of RBV dosing may be done sooner if the rash worsens despite discontinuation of telaprevir. Peg-IFN-alfa may be continued unless interruption is medically indicated.

Resumption of treatment: telaprevir dosing cannot be restarted after having been discontinued due to an adverse event. Peg-IFN-alfa and/or RBV may be restarted, if interrupted due to rash, if there is improvement in the rash within 14 days following their respective discontinuation. RBV monotherapy is not allowed; therefore, if Peg-IFN-alfa and RBV dosing are interrupted and RBV is restarted, Peg-IFN-alfa must also be restarted.

### **9.3.1.1.3.2. Management of Grade 3 Rash**

General recommendations: For subjects experiencing a grade 3 rash, the same general recommendations as for subjects experiencing grade 1 and grade 2 rashes apply.

Treatment discontinuation: In subjects experiencing a grade 3 rash, telaprevir should be discontinued immediately and permanently. If the rash does not improve, symptomatically or objectively, within 7 days following telaprevir discontinuation, RBV use should also be interrupted. Interruption of RBV dosing may be done sooner if the subject's rash worsens despite discontinuation of telaprevir. Peg-IFN-alfa may be continued unless interruption is medically indicated. The investigator may discontinue telaprevir, Peg-IFN-alfa, and RBV simultaneously if clinically indicated.

However, any subject diagnosed with or suspected to have DRESS, EM, or AGEP must have telaprevir, Peg-IFN-alfa, and RBV discontinued immediately and permanently.

Resumption of treatment: telaprevir dosing cannot be restarted after having been discontinued due to grade 3 rash. Peg-IFN-alfa and/or RBV may be restarted, if interrupted due to grade 3 rash, if there is improvement in the rash within 14 days following the interruption. RBV monotherapy is not allowed; therefore, if Peg-IFN-alfa and RBV dosing are interrupted and RBV is restarted, Peg-IFN-alfa must also be restarted. Please note that any subject who discontinues treatment due to DRESS, EM, or AGEP should not resume telaprevir, Peg-IFN-alfa, or RBV.

Management: The sponsor's physician responsible for the early access program should be notified immediately of any subject who is diagnosed with or suspected to have DRESS, EM, or AGEP. The rash pages in the CRF must be completed.

Referral to a dermatologist is recommended for all grade 3 rashes. The following laboratory tests are mandatory: the hematology tests (with differential) described in Section 9.3, ALT, AST, and creatinine. Any additional or subsequent laboratory testing should be performed as needed, eg, if rash is worsening or if significant laboratory abnormalities that are identified, require monitoring.

Close clinical follow-up and appropriate medical intervention should be instituted. Daily follow up, in person or by telephone, to monitor for progression of the event may be necessary from the onset of the event until improvement is observed. Additional visits should be performed (eg, each week or more often, as clinically appropriate). All subjects should be followed until rash has resolved completely.

### **9.3.1.1.3.3. Management of Grade 4 Rash**

General recommendations: For subjects experiencing a grade 4 rash, the same general recommendations as for subjects experiencing grade 1, 2, and 3 rashes apply.

Treatment discontinuation: Subjects diagnosed with or suspected to have a skin rash that is considered life-threatening (grade 4 rash), including SJS and TEN, must have telaprevir, Peg-IFN-alfa, and RBV discontinued immediately and permanently.

Resumption of treatment: Any subject who discontinues telaprevir, Peg-IFN-alfa, and RBV due to a grade 4 rash cannot resume treatment.

Management: The sponsor's physician responsible for the early access program should be notified immediately of any subject who is diagnosed with or suspected to have a skin rash that is considered life-threatening (grade 4 rash), including SJS and TEN. The rash pages in the CRF must be completed.

Referral to a dermatologist is recommended for all grade 4 rashes. The following laboratory tests are mandatory: the hematology tests (with differential) described in Section 9.3, ALT, AST, and creatinine. Any additional or subsequent laboratory testing should be performed as needed, eg, if rash is worsening or if significant laboratory abnormalities that are identified, require monitoring.

Close clinical follow-up and appropriate medical intervention should be instituted. Daily follow up, in person or by telephone, to monitor for progression of the event may be necessary from the onset of the event until improvement is observed. Additional visits should be performed (eg, each week or more often, as clinically appropriate). All subjects should be followed until rash has resolved completely.

### **9.3.1.2. Management of Anemia**

Decreases in hemoglobin levels are commonly observed in the treatment of chronic HCV infection. Hemoglobin levels should therefore be assessed before treatment and at Weeks 2, 4, 8, and 12, and as clinically appropriate thereafter. In certain cases it may be indicated to follow these parameters more frequently; this will be at the discretion of the investigator and unscheduled visits can be performed.

If anemia develops during treatment, treatment modifications of RBV should be made in line with label recommendations. Note that if RBV is permanently discontinued for the management of anemia, telaprevir must also be permanently discontinued. Telaprevir dose reductions are prohibited and once telaprevir treatment is discontinued for the management of anemia, it may not be reinitiated.

Anemia which occurs between the first use of investigational product (telaprevir) and 30 days after administration of the last dose of telaprevir will be recorded in the CRF (see Section 12.3.1) according to DAIDS criteria (see Attachment 3).

All interventions for anemia should be recorded on the CRF as described in Section 8, Prestudy and Concomitant Therapy.

## **10. SUBJECT COMPLETION/WITHDRAWAL**

### **10.1. Completion**

A subject will be considered to have completed the early access program if he or she has completed assessments at Week 24 or 48, based on virologic response to treatment as measured by locally collected plasma HCV RNA levels and/or type of subject (treatment naïve or prior treatment relapsers, or previously treated with prior partial or prior null response, or who had viral breakthrough; and Metavir/Ishak score) as discussed in Section 3.1, Study Design.

### **10.2. Discontinuation of Treatment**

If a subject's study treatment (telaprevir) must be discontinued before the end of the treatment regimen, this will not result in automatic withdrawal of the subject from the early access program.

A subject's treatment (telaprevir, Peg-IFN-alfa, RBV) may be discontinued if:

1. an serious adverse event occurs  
(Note: treatment must be discontinued for skin reactions considered serious adverse events, as described in the table below);
2. they fail to comply with the protocol requirements or fail to cooperate with the investigator.

A subject's treatment with telaprevir may be permanently discontinued if a subject develops a medical condition that requires concomitant therapy with a prohibited drug listed in Section 8.

Subjects must discontinue telaprevir and Peg-IFN-alfa/RBV or have their treatment modified for the reasons included in the table below.

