## **8. PRESTUDY AND CONCOMITANT THERAPY**

The use of all therapy for hepatitis C infection (eg, Peg-IFN-alfa, RBV), prior to and during the early access program, should be recorded in the case report form (CRF).

Use of all therapy (prescription and over-the-counter) for rash and anemia administered after the first use of telaprevir until 30 days after administration of the last dose of telaprevir should be recorded on the appropriate pages of the CRF. See Section 9.3.1.1.2 for additional information on allowed and prohibited concomitant therapies for treatment of rash.

For serious adverse events, concomitant medications will be recorded in the CRF.

For therapies listed above, the therapy, start and stops dates, dosing regimen, route of administration, and dosage changes will be recorded in the CRF. All other concomitant medication should be recorded in the subject's medical record.

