### **Recommendations for Other Medicinal Products**

Recommendations for other medicinal products, as a result of drug interactions with telaprevir, are provided in Attachment 2. These recommendations are based on either drug interaction studies or predicted interactions due to the expected magnitude of interaction and potential for serious adverse events or loss of efficacy. Attachment 2 is a comprehensive list of all recommendations, however, since co-infections with active hepatitis B and HIV are excluded, antiviral treatments are not allowed.

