**Concomitant therapy with any of the following should not be prescribed.**

#### **CYP3A substrates with a narrow therapeutic index**

Telaprevir must not be administered concurrently with medicinal products with a narrow therapeutic window that are substrates of cytochrome P450 3A (CYP3A). Co-administration of telaprevir may increase the plasma concentration of these medicinal

products, which may lead to serious and/or life threatening adverse reactions such as cardiac arrhythmia (ie, amiodarone, astemizole, bepridil, cisapride, flecainide, pimozide, propafenone, quinidine, terfenadine), or peripheral vasospasm or ischemia (ie, dihydroergotamine, ergonovine, ergotamine, methylergonovine), or myopathy, including rhabdomyolysis (ie, lovastatin, simvastatin), or prolonged or increased sedation or respiratory depression (ie, orally administered midazolam, triazolam), or hypotension, or cardiac arrhythmia (ie, alfuzosin and sildenafil for pulmonary arterial hypertension).

Telaprevir must not be administered concurrently with any Class I or III antiarrhythmics.

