#### St. John's wort (*Hypericum perforatum*)

Plasma concentrations of telaprevir can be reduced by concomitant use of the herbal preparation St. John's wort (*Hypericum perforatum*). Therefore, herbal preparations containing St. John's wort should not be combined with telaprevir.

The decision to administer a prohibited drug or treatment during telaprevir administration should be discussed with the sponsor's responsible physician for the early access program.

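### The bar on co-administering prohibited drugs in Section 8 does not match the discussion route that closes that section or the optional stopping in Section 10.2, and loratadine is missing from both lists it is referred to.

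*Protocol*

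**What the plan says.** Section 8 gives the bar in its strongest form for two groups: "Telaprevir must not be administered concurrently with medicinal products with a narrow therapeutic window that are substrates of cytochrome P450 3A (CYP3A") and "Telaprevir must not be administered concurrently with any Class I or III antiarrhythmics". Rifampicin also carries *must not*. St. John's wort carries *should not*, as does the sentence introducing the whole list. Section 4.3 sends the reader to Section 8 for the contraindications to telaprevir.

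The last paragraph of Section 8 reads: "The decision to administer a prohibited drug or treatment during telaprevir administration should be discussed with" the sponsor's responsible physician.

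Section 10.2 says that "treatment with telaprevir may be permanently discontinued if a subject develops a medical condition that requires concomitant therapy with a prohibited drug", and limits this to drugs listed in Section 8. The sentence after it uses *must* for the reasons in the table that follows.

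Section 9.3.1.1.2 prohibits three antihistamines from 14 days before Day 1 until 7 days after the last telaprevir dose: "astemizole, terfenadine, and loratadine (see Section 8 and Attachment 2"). Of the attachment, Section 8 says "Attachment 2 is a comprehensive list of all recommendations".

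On data capture, Section 8 sends to the CRF all hepatitis C therapy, therapy for rash and anemia, and concomitant medication for serious adverse events. "All other concomitant medication should be recorded" in the medical record.

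**The concern.** An investigator whose patient comes to need a prohibited drug gets three different signals: the two must not be combined, combining them is something to discuss, and stopping telaprevir is optional. For the CYP3A group the protocol's own reason for the bar is the risk of serious or life-threatening reactions, so this is a patient-safety rule on which sites could act differently while each follows the text.

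The loratadine gap matters because antihistamines are a class that the protocol itself allows for rash, and rash is an adverse event of special interest. A site checking Section 8 or Attachment 2 before prescribing would not learn that loratadine is barred. A site screening from Section 4 would not learn of the 14-day window.

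**Working it through.** No figure in the plan depends on this point, so the check compares texts.

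**1. Strength of the bar by group.** The CYP3A paragraph of Section 8 names 9 drugs for arrhythmia, 4 for vasospasm or ischemia, 2 for myopathy, 2 for sedation or respiratory depression, and 2 for hypotension or arrhythmia: 9 + 4 + 2 + 2 + 2 = 19. Two of these are restricted: midazolam to the oral route, sildenafil to pulmonary arterial hypertension.

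| Group | Wording of the bar | Reason given | Reached by the Section 10.2 sentence? |
|---|---|---|---|
| Narrow-index CYP3A substrates (19 named) | *must not* | serious or life-threatening reactions | yes, telaprevir *may* be stopped |
| Class I or III antiarrhythmics | *must not* | none stated separately | yes, *may* |
| Rifampicin | *must not* | telaprevir AUC lowered by about 92% | yes, *may* |
| St. John's wort | *should not* | telaprevir concentrations can fall | yes, *may* |
| Loratadine | prohibited, in Section 9.3.1.1.2 only | none stated | no, not listed in Section 8 |

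**2. Bar against discussion route.** The closing paragraph of Section 8 speaks of a decision to administer a prohibited drug during telaprevir. It does not separate the *must not* groups from the *should not* group, and the discussion itself is only a *should*.

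**3. Bar against discontinuation rule.** The Section 10.2 sentence applies only when the condition requires the prohibited drug. If telaprevir is then kept and the required drug is given, the two are taken together, which Section 8 rules out for three of its four groups. Section 6 prohibits telaprevir dose modification, and I find no provision for pausing it. In the table of mandatory reasons, treatment with systemic corticosteroids has its own row; the need for a Section 8 drug has none.

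**4. Lists.** Of the three antihistamines in Section 9.3.1.1.2, Section 8 names astemizole and terfenadine. Attachment 2 has no antihistamine heading and names none of the three.

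**5. Window.** Day -14 appears in Section 9.3.1.1.2. It does not appear in Sections 4.1 to 4.3 or in Section 8. Section 9.1.2 and footnote a of the Time and Events Schedule allow the interval from screening to Day 1 to be shortened, with no 14-day minimum.

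**The case against.** The best defence is that these sentences do different jobs. The discussion sentence can be read as a control rather than a permission: Section 17.1 has the same route for any unavoidable departure, with sponsor contact beforehand except in emergencies. Likewise, Section 10.2 names a permitted reason for stopping telaprevir and nowhere authorises giving both drugs. The loratadine problem can be called a cross-reference slip, since the prohibition itself is explicit and four permitted antihistamines are named beside it. Attachment 2 omits astemizole and terfenadine too, so it looks more like a table of interaction recommendations than the list of prohibited drugs.

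Much of this is fair. A reader might infer that the protocol permits co-administration; it does not say so. What remains is that the text does not settle the matter. *May*, attached to a drug that is required, leaves open what follows if telaprevir is not stopped. The control reading of the discussion sentence has to be supplied by the reader. A slip in a cross-reference to a prohibition still sends the site to lists that lack the drug.

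A reader might also infer that a prohibited drug given after discussion would be missing from the database, and that the resulting events would be counted as telaprevir tolerability. The protocol does not support that as a general claim. Section 17.1 requires CRF data to reflect any departure from the protocol. Drugs given for rash, anemia or serious adverse events are captured under Section 8, which covers loratadine given for rash and concomitant medication for the most serious interactions. The attribution definitions in Section 12.1.2 let the investigator name a concomitant drug as the alternative explanation. The residue is narrow: it is unclear whether use agreed through the Section 8 discussion route still counts as a departure.

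**Conclusion.** The inconsistency is real and should be corrected. *Must not* in Section 8, the discussion sentence in the same section and *may* in Section 10.2 do not form one rule. Loratadine and its Day -14 window are missing from the places where a site would look for them.

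Its size cannot be given. The roughly 3,000 planned subjects are the population under the rule, and a reader might take that as the number affected. Only those who come to need or take such a drug are affected, and the protocol states no frequency of use. Nor does the life-threatening rationale extend to every listed drug: the protocol gives it for the CYP3A group, while for rifampicin and St. John's wort the stated reason is lower telaprevir exposure.

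The conclusion rests on the protocol text alone. It takes no view on which clinical rule is right, and it implies no error in the planned safety estimates.

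**What to change.** Reconcile Section 8 (the prohibitions and the closing paragraph), Section 9.3.1.1.2 and Section 10.2. For each drug group, state the strength of the bar, whether discussion with the sponsor's physician can alter it, and what follows for telaprevir if the drug is required. The Section 10.2 sentence and its table should then express that same rule. Make the lists in Section 8 and Attachment 2 agree with Section 9.3.1.1.2, and carry the Day -14 window consistently through Sections 4, 8 and 9.3.1.1.2. The content of each rule is for the sponsor's clinicians.

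As a minor addition, state in Section 8 that co-administration agreed with the sponsor is also recorded in the CRF, so that capture does not depend on whether it counts as a departure under Section 17.1.

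The cost is amendment wording, with the ethics committee review that Section 17.1 requires, and at most one CRF field. The sample size and the planned analyses do not change.
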